### Subgroup analyses

ANCOVA/Non-Parametric ANCOVA: Subgroup analyses will be conducted using ANCOVA or non-parametric ANCOVA depending on the normality of the data. Subgroups may include stratification by age, educational attainment, religion, and employment status.Multiple Comparisons: To address the risk of type I error due to multiple comparisons, appropriate statistical corrections will be applied, which may include the Bonferroni correction, Holm’s adjustment, or the Benjamini-Hochberg procedure.

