Does learning the Bhagavad Gita reduce psychological distress in people experiencing homelessness	The immediate post-intervention, delayed post-intervention, and long-term follow-up Kessler psychological distress scale scores will be significantly lower than baseline Kessler psychological distress scale scores	54 participants each in the Bhagavad Gita group, Kuchipudi dance group, Both Bhagavad Gita and Kuchipudi dance group, and Control group for 80% power and 5% alpha	The within-group differences will be analysed by repeated measures analysis of covariance, with continued practice and religion as covariates. Subgroup analyses will be conducted by stratifying the participants in each group by age, religion (Hindu, Non-Hindu), educational attainment, and employment. Post-hoc power analyses will be conducted to verify the robustness and reliability of the subgroup analyses	If we find significant within-group differences in the Kessler psychological distress scale scores, it would suggest that learning the Bhagavad Gita has a potential impact on reducing psychological distress in people experiencing homelessness. Additionally, if our subgroup analyses reveal significant differences based on age, religion, educational attainment, and employment, it would imply that the intervention’s effectiveness varies across these subgroups

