### Statistical methods

#### Data analysis

All results will be reported in accordance with the CONSORT guidelines to ensure comprehensive and transparent reporting of the trial’s outcomes. Descriptive summaries of baseline characteristics will be presented to provide an overview of the study population. The comparisons will be between each intervention group and the control group, as well as within each intervention group over time. The repeated measures data will be analysed using the generalised estimating equation (GEE) framework. For the analysis of the primary outcome using the GEE framework, robust standard errors will be used to account for correlated data. Pairwise post-hoc comparisons will be conducted to identify specific group differences. To control for the risk of type I error in these multiple comparisons, the Bonferroni correction will be applied. Subgroup analysis will be conducted using analysis of covariance (ANCOVA) or non-parametric ANCOVA [19] depending on the normality of the data; this may include stratification by age, educational attainment, religion, and employment status. Multiple comparisons will also be addressed using appropriate statistical corrections. These may include the Bonferroni correction, Holm’s adjustment, or the Benjamini-Hochberg procedure, depending on the specific comparisons and the number of tests conducted. The data analysis will be conducted using Python 3.9.13. Statistical significance will be set at a two-tailed p < 0.05.

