### Sensitivity analyses

Robustness Checks: Sensitivity analyses will be performed to assess the robustness of the primary findings. Analyses will include different imputation methods for missing data and alternative statistical models (e.g., mixed-effects models).Assumption Testing: Assumptions of the GEE and ANCOVA models will be tested, including the assumption of normality and homogeneity of variances. Alternative models or transformations will be used if assumptions are violated.Exclusion of Outliers: Sensitivity analyses will be conducted with and without outliers to determine their impact on the study results.

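### The subgroup analysis method is picked by the normality of the data: a poor rule which, if applied stratum by stratum, can leave compared strata analysed by different methods

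*Protocol article*

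**What the plan says.** The rule appears twice in the protocol article. The Data analysis section gives the subgroup method as "analysis of covariance (ANCOVA) or non-parametric ANCOVA [19] depending on the normality of the data". The Subgroup analyses section of the SAP repeats it: "Subgroup analyses will be conducted using ANCOVA or non-parametric ANCOVA depending on the normality of the data". The non-parametric method is identified only by a citation.

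The Sensitivity analyses section says how normality will be judged and what follows: "Assumptions of the GEE and ANCOVA models will be tested, including the assumption of normality and homogeneity of variances", and "Alternative models or transformations will be used if assumptions are violated". It names no test, no cut-off and no level (whole data set, factor or stratum) at which the check is made.

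Table 1, in the Introduction, sets the structure and the use of the results. On structure: "Subgroup analyses will be conducted by stratifying the participants in each group by age, religion (Hindu, Non-Hindu), educational attainment, and employment". On use, if these analyses show significant differences, "it would imply that the intervention’s effectiveness varies across these subgroups".

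The Primary analysis section handles the same K10 outcome by GEE with robust standard errors, and does not make the choice of that method depend on normality.

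**The concern.** There are two problems, one unconditional and one conditional.

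1. **The rule selects badly on any reading.** Non-normality threatens mean-based ANCOVA mainly in small samples, yet a normality test has little power there and high power in large ones. The switch therefore tends to abandon ANCOVA where it is safest and keep it where non-normality could do harm. The estimand of each subgroup analysis is also left to be settled by the outcome data.

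2. **If the check is made stratum by stratum, compared strata may lack a common effect measure.** Table 1 wants to conclude that effectiveness varies across strata. If one stratum is analysed by ANCOVA in K10 points and the other by the non-parametric method, an apparent difference between them, or its absence, can come from the method alone.

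A related loss arises on either reading. Unless the cited method yields mean differences, which the article does not say, a switched result has no K10-point effect to set against the primary GEE estimates or the 7-point difference in the Sample size calculation.

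**Working it through.** The plan gives no figure on this point, so there is none to reproduce. The check asks how often the rule would switch, and how often it would treat two compared strata differently.

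**Inputs from the article.** 54 participants per group and four groups (Sample size calculation). Two arms give 2 × 54 = 108 people; all four give 4 × 54 = 216. Significance: "Statistical significance will be set at a two-tailed p < 0.05".

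**Assumptions, because the article gives none.** Shapiro-Wilk at 0.05 as the test. K10 as integers from 10 to 50, with the same distribution in both strata. Strata of 80/20 (86 v 22 of 108; 173 v 43 of 216) and 90/10 (97 v 11; 194 v 22).

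**Step 1: how the switch depends on sample size.** Share of 3,000 simulated samples in which normality is rejected:

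| K10 shape | n = 20 | n = 54 | n = 108 | n = 216 |
|---|---|---|---|---|
| Near normal (mean 25, SD 7) | 5% | 5% | 8% | 22% |
| Mild skew (10 + gamma(6, 2.5)) | 22% | 59% | 91% | 99.9% |
| Moderate skew (10 + gamma(2.5, 4)) | 45% | 93% | 99.9% | 100% |

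With the distribution held fixed, sample size alone moves the rule from ANCOVA to the non-parametric method.

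**Step 2: if each stratum is tested separately.** With rejection probabilities p₁ and p₂ in two independent strata,

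P(different methods) = p₁(1 − p₂) + p₂(1 − p₁).

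- Two exactly normal strata: 2 × 0.05 × 0.95 = 0.095. About 9.5% is therefore the background rate.
- Mild skew, 173 v 43, p₁ = 0.9905 and p₂ = 0.4735: 0.9905 × 0.5265 + 0.4735 × 0.0095 = 0.526 (simulated directly: 0.525).
- Mild skew, 194 v 22, p₁ = 0.998 and p₂ = 0.2415: 0.998 × 0.7585 + 0.2415 × 0.002 = 0.757 (simulated directly: 0.7575).

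For one intervention group against control (108 people, 2,000 runs per setting):

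| K10 shape | 86 v 22 | 97 v 11 |
|---|---|---|
| Normal, mean 20, SD 7, cut at the floor of 10 | 68% | 78% |
| Mild skew (10 + gamma(4, 3)) | 64% | 82% |
| Moderate skew (10 + gamma(2, 5)) | 40% | 70% |
| Normal, mean 28, SD 7 | about 10% | about 10% |

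An independent re-run gave 66%, 65% and 40% for 86 v 22, 79%, 81% and 72% for 97 v 11, and 9% to 10% for the normal with mean 28.

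**Step 3: sensitivity to the assumptions.**

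- *Position relative to the floor.* For a normal with SD 7 and 86 v 22, discordance falls from about 68% at mean 20 to 29% at mean 22 and about 12% at mean 24.
- *Residuals instead of raw scores.* With a baseline correlation of 0.5, the floor-limited case (mean 20) falls to about 20%. With skewed scores discordance persists, at 58% to 86%.
- *Equal strata (108 v 108).* 14% near normal, 17% mild skew, 0.2% moderate skew.

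**Step 4: if normality is checked once on the pooled data.** Discordance between strata is zero by construction. The n = 216 column of Step 1 shows that the method would then be settled by the shape of K10: switched in 22% of trials with near-normal scores and in almost all with skewed ones.

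**The case against.** A reader might infer that large strata will be analysed on ranks and small ones on means. The documents do not support that as stated. Nothing says the check is run stratum by stratum; a single check per factor or on the whole data set fits the wording equally well and puts all strata on one method. Nor is a rank scale stated: the alternative is identified only by citation, and not every non-parametric ANCOVA is rank-based. Both parts of the objection stand, so the mismatch between strata is a conditional consequence.

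It can also be said that the Sensitivity analyses section ties normality to the ANCOVA model, which suggests residuals and not raw K10. That is a fair reading. It removes most of the problem in the floor-limited case but not in the skewed cases.

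The percentages also depend on assumed shapes and splits, and some of the low ones are no more than the background disagreement of two 5% tests. That stands too.

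Finally, the analyses are exploratory, and a condensed article may leave the test and cut-off to a fuller plan. This limits the weight of the point but does not answer it. The complaint is not that a criterion is missing: the article states a rule, twice, and the rule is a poor one whatever test and cut-off are filled in.

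**Conclusion.** The point holds in a limited form. The article makes the subgroup method depend on a normality check of the trial's own data, and such a check tends to switch where switching is least needed. That part rests only on the text and on the behaviour of normality tests.

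That compared strata would be analysed by different methods is conditional on checking each stratum separately. On that reading, for 108 people split 80/20 to 90/10, it occurs in about 40% to 82% of trials with skewed or floor-limited K10 and in about 10% with near-normal K10. It is also uncommon when strata are equal in size. On the pooled reading it does not occur, but the method remains data-dependent and the effect may not be in K10 points.

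It should be corrected before analysis because Table 1 attaches a conclusion about varying effectiveness to these results. It does not touch the primary GEE comparison, which this rule does not govern.

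**What to change.** In the Data analysis section, delete "or non-parametric ANCOVA [19] depending on the normality of the data", and delete the matching phrase in the Subgroup analyses section. In their place:

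- Pre-specify one mean-based model for all subgroup factors: either the primary GEE specification, or baseline-adjusted ANCOVA with robust standard errors. Add a small-sample correction, because uncorrected robust standard errors are unreliable in strata as small as about 11.
- Fit it to all participants with a treatment-by-subgroup interaction. A common scale alone does not support Table 1's inference that effectiveness varies; the interaction is the test of that.
- Report stratum effects and interaction estimates in K10 points with confidence intervals.
- If non-parametric ANCOVA is wanted, run it in every stratum as a labelled sensitivity analysis, not triggered by a test.

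With the method fixed in advance, the chance that two compared strata are analysed by different methods is zero on either reading. The cost is a change of wording in two sections, with no new data. The downside is that intervals in very small strata remain approximate, and they should be labelled so.

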### Sensitivity analyses

Robustness Checks: Sensitivity analyses will be performed to assess the robustness of the primary findings. Analyses will include different imputation methods for missing data and alternative statistical models (e.g., mixed-effects models).Assumption Testing: Assumptions of the GEE and ANCOVA models will be tested, including the assumption of normality and homogeneity of variances. Alternative models or transformations will be used if assumptions are violated.Exclusion of Outliers: Sensitivity analyses will be conducted with and without outliers to determine their impact on the study results.

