### Outcomes and measures

The primary outcome is psychological distress measured by the Kessler scale of psychological distress (K10) in this study. The K10 is a 10-item questionnaire that measures psychological distress based on questions about anxiety and depressive symptoms. It has previously been used in research conducted with PEH [17, 18]. At the immediate post-intervention, delayed post-intervention, and long-term follow-up measurements, apart from the K10, the participants will be asked if they have continued practicing the techniques learned during the intervention (Kuchipudi group: continued practice of the choreography, Gita group: continued self-reflection on the teachings of the Bhagavad Gita, Both group: continued practice of the choreography and continued self-reflection on the teachings of the Bhagavad Gita, and control group: none). The study flowchart is presented in Fig 2.

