#### Sample size calculation

The required sample size for GEE was calculated using the formula,

$$n=[(Z\alpha /2+Z\beta {)}^{2}*V\_eff]/(\Delta^{2}*\rho^{2}),$$

where n is the required sample size per group; Zα/2 is the critical value of the standard normal distribution for a two-tailed test with a significance level of α; Zβ is the critical value of the standard normal distribution for a specified power (1-β) of the test; V_eff is the effective sample size, which accounts for the correlation between the repeated measures within individuals; Δ is the minimum clinically significant difference; r is the number of repeated measures; and ρ is the correlation between the repeated measures.

Assuming a conservative value of 0.5 for ρ based on previous literature [20, 21], and for an α of 5%, 1-β of 80%, r of 4, and Δ of 7 [22, 23], we can calculate the effective sample size as follows:

$$\begin{array}{l} V\_eff=n/(1+(r‐1)*\rho )\\ \;=55/(1+(4‐1)*0.5)\\ \;=22.5 \end{array}$$

Therefore, n can be calculated as follows:

$$\begin{array}{l} n=[(1.96+0.84{)}^{2}*22.5]/(7^{2}*0.5^{2})\\ \;=53.3 \end{array}$$

Thus, at least 54 participants per group must be enrolled to have 80% power to detect a minimum clinically significant difference of 7 points between the groups using GEE, with a significance level of 5%. As there are four groups in the study, a total of 216 participants (54 per group) must be enrolled. Based on our previous experience, a dropout rate of 16% was expected; to account for this, we aim to recruit a total of 256 participants, with 64 participants per group.

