### Primary analysis

GEE Framework: The primary outcome, psychological distress as measured by the K10 scale, will be analyzed using the GEE framework. Robust standard errors will be used to account for correlated data due to repeated measures. An exchangeable correlation structure will be assumed.Primary Comparisons: Comparisons will be made between each intervention group (Gita, Kuchipudi, and Both) and the control group. Within each intervention group, comparisons over time (pre-intervention, immediate post-intervention, 40 days post-intervention, and 1-year post-intervention) will be performed.Pairwise Post-Hoc Comparisons: Pairwise post-hoc comparisons will be conducted following significant GEE results to identify specific group differences. The Bonferroni correction will be applied to control for the risk of type I error in these multiple comparisons.

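### Normality and equal variances are listed as assumptions of the GEE, which needs neither with robust standard errors, and the rule that follows leaves unclear whether the primary model stands if the checks fail

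*Protocol article*

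**What the plan says.** The Primary analysis section fixes the model: "The primary outcome, psychological distress as measured by the K10 scale, will be analyzed using the GEE framework". It adds "Robust standard errors will be used to account for correlated data due to repeated measures" and "An exchangeable correlation structure will be assumed". No condition is attached.

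The Sensitivity analyses section then says, under its assumption-testing item, "Assumptions of the GEE and ANCOVA models will be tested, including the assumption of normality and homogeneity of variances". The next sentence gives the consequence: "Alternative models or transformations will be used if assumptions are violated". It names no test, threshold, replacement model or transformation.

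The subgroup analyses already have their own normality rule: "Subgroup analyses will be conducted using ANCOVA or non-parametric ANCOVA depending on the normality of the data".

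The Sample size calculation defines the target effect in raw score units. The trial is sized "to detect a minimum clinically significant difference of 7 points between the groups using GEE".

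**The concern.** A GEE with robust standard errors rests on a correctly specified mean model and enough independent participants. The robust variance is used precisely so that the working variance and correlation need not be right. Normality of the outcome and equal variances are classical assumptions of ANCOVA, not of this estimator. Listing them for the GEE is a misstatement, not an omitted detail.

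The misstatement matters because an action is tied to it. If the rule reaches the primary model, a test result unrelated to the validity of the GEE could lead to another model, chosen once the data are in view. A log or rank analysis, for example, would not give an estimate in K10 points, so it could not be read against the 7-point difference. The Timeline section also has an interim analysis in Weeks 13–19 and a final one in Weeks 57–61, so the check could be made twice with different outcomes.

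**Working it through.** **Plan's own figure.** The plan gives no figure on this point. Its planned size, 54 per group and 216 in total, is used below only as a sample size. (The displayed formula gives 2.8² × 22.5 / (7² × 0.5²) = 176.4 / 12.25 = 14.4, not 53.3. That is a separate matter and has no bearing here.)

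**Inputs from the document.** Four groups of 54, four visits, within-person correlation 0.5, two-sided 5% level, and a 7-point difference.

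**Inputs assumed.** The document says only that "The K10 is a 10-item questionnaire that measures psychological distress based on questions about anxiety and depressive symptoms". The following are therefore assumptions:
- a score range of 10 to 50 (ten items scored 1 to 5)
- rounded beta-distributed scores
- means of 16 to 35 and SDs of 5 to 9
- Shapiro-Wilk and median-centred Levene tests at 5%

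**1. How often a normality test rejects with no effect.** One visit, 216 participants, SD 6 to 9, 1,000 samples per setting:

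| Mean K10 | Rejection |
|---|---|
| 16 to 22 | 100% |
| 25 | 80–100% |
| 28 | 35–99% |
| 30 | 29–97% |

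In a single arm of 54 the rates are 77–100% at means of 16 to 20 and 40–94% at a mean of 22. A second simulation used residuals from the four-arm, four-visit layout and a wider SD range (200 runs per setting). At one visit it also gave 100% at means of 16 to 20. With an SD of 5 it gave only 40% at a mean of 25 and 10% at a mean of 30. Scores built from ten graded items, with means of about 16 to 33, gave 86–100% at one visit.

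**2. Normality or equal-variance test, with and without a 7-point effect.** Over 30 scenarios with all 864 residuals pooled (216 × 4), one test or the other rejected in at least 86% of runs in 28 scenarios. The exceptions were 44% and 47%. Using residuals from one visit for the normality test, rejection was at least 50% in 24 scenarios and 12–46% in the other six.

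**3. Equal-variance test alone.** With no effect, Levene rejected in 2–7% of runs, about its nominal rate. When a 7-point effect moved a baseline mean of 20 to 13, close to the assumed floor, it rejected in 60–100%. From baseline means of 25 or more the same effect gave 2–12%. The SD was held at its baseline value in these runs, so the high rates reflect the change of shape as scores pile up at the floor.

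**4. Whether the robust comparison needs rescue.** Two arms of 54, no effect, skewed bounded scores:
- Unequal-variance t-test at one visit, 20,000 runs: 4.96% (mean 16, SD 6), 5.01% (20, 7), 4.83% (22, 8), 5.03% (25, 8).
- Robust Wald test, 4,000 runs per setting: 5.3–5.8% for change from baseline and 5.1–5.5% for the level at one visit, with skewness from −0.16 to 1.2. With complete data and a separate mean for each arm and visit, the GEE estimate is the difference in means, so this is the planned type of test.

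The small excess in the Wald test is not caused by skewness. On exactly normal scores, a variance with divisor 54 and a cut-off of 1.96 corresponds to a t statistic on 106 degrees of freedom beyond 1.96 × √(53/54) = 1.942, which has probability 5.5%.

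**The case against.** **Placement.** The sentence sits under Sensitivity analyses. That section opens by describing checks on the primary findings, and its neighbouring items (mixed-effects models, outlier exclusion) are plainly supplementary. The Primary analysis section is unconditional. On this reading, other models are added beside the GEE and nothing is replaced. This stands as a fair reading, and a reader who infers that the plan drops its primary GEE when a test fails goes beyond the text. But the sentence names the GEE, is worded as something that will happen, and is not limited to supplementary work, and nothing says that the GEE stays primary.

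**Shared list.** The two assumptions could be meant for ANCOVA only. That is possible, but the sentence assigns them to both models, and ANCOVA already has its own normality rule for the subgroups.

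**Assumed inputs.** The rejection rates depend on a test, range, means and SDs that the document does not give. The near-certain rates belong to low means, whereas the Introduction describes heightened distress in this population. On a floor of 10, a mean of 16 could not fall by 7 points at all. This stands: at mid-scale means with a small SD the test often passes.

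**Blinding.** The research team, which analyses the data, is to be blinded to allocation. That limits choosing a model to favour an arm. It does not settle which analysis is primary.

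**Article format.** An unnamed test or alternative model may be left to a fuller plan, and is not counted here. The point concerns a statement that is made and is wrong.

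**Conclusion.** The point holds in a limited form. Normality and homogeneity of variances are wrongly given as GEE assumptions, and the action tied to them leaves the status of the primary model ambiguous. The documents do not establish that the GEE would be replaced, only that the wording permits that reading.

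Nor do they support saying that the checks would fail whatever the treatment does. A normality test would reject in most of the settings tried even with no effect, but not in all. The equal-variance test rejects at about 5% with no effect and more often when an effect moves scores toward the floor, so that part of the trigger can depend on treatment. These rates rest on the assumed K10 distributions and tests.

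The conclusion that no switch is needed is firmer: robust comparisons kept type I error at about 5–6% in every setting tried, although those runs assumed complete data. The correction is worth making because it concerns the primary analysis and costs almost nothing.

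**What to change.** In the assumption-testing item of the Sensitivity analyses section:
- Limit the normality and equal-variance checks to the ANCOVA analyses.
- State that the GEE on untransformed K10 points with robust standard errors remains the primary analysis whatever those checks show.
- Report any transformed or alternative model, including the mixed-effects model already listed, only as a labelled sensitivity analysis beside it.

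This takes one or two sentences and needs no further data. The price is giving up the freedom to switch the primary model.
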